## Abstract

**Background::**

End-to-end anastomosis to the internal mammary artery (IMA) is the current standard anastomosis technique for women undergoing autologous breast reconstruction with deep inferior epigastric perforator (DIEP) flap. This approach fails to preserve the length of the IMA, compromising its availability for cardiac surgery use in women who develop coronary heart disease. A viable alternative may be end-to-side anastomosis, but data on its feasibility is currently lacking.

**Methods::**

This pilot study will involve 60 patients at a single-center institute over approximately 24 months. Inclusion criteria are female sex, age >18 years, history of breast cancer, and eligibility for unilateral autologous DIEP breast reconstruction. Exclusion criteria include patients with a legal guardian, inability to consent, and history of blood clotting disorders or hypercoagulability. Data will be collected at 2 weeks, 6 weeks, 6 months, and 1-year post-surgery. The primary outcome is “major complication” of the recipient site, including anastomotic insufficiency, arterial thrombosis, hematoma, reoperation, or flap loss. Secondary outcomes are abdominal perfusion and major donor site complications, such as wound healing disorders. Patient satisfaction will be assessed using the SF-36 and BREAST-Q (reconstructive module) questionnaires.

**Study status::**

The DIEP-ES study has begun enrolment in February 2023. As this is an ongoing trial, no results have been gathered yet. The results will be reported upon completion of the study. We anticipate that the primary and secondary outcomes of the end-to-side approach will be comparable to the accepted standard of care, i.e., end-to-end anastomoses.

**Conclusions::**

End-to-side anastomosis may be a safe alternative for DIEP breast reconstruction, especially for patients at risk for coronary heart disease. This pilot study aims to evaluate the feasibility and safety of the end-to-side anastomosis technique in DIEP-flap breast reconstruction. The preliminary findings will inform the design of future multicentric trials to confirm the efficacy of this approach.

## Introduction

According to the World Health Organization, breast cancer is currently the most prevalent cancer worldwide; in 2020 alone, 2.3 million women received a new diagnosis, while by the end of the same year, there were 7.8 million women who had been diagnosed with breast cancer since 2015. In terms of quality of life, more disability-adjusted life years are lost by women due to breast cancer than any other type of cancer globally.^[^1^]^ Previous studies outlined that breast reconstruction does not just improve patient quality of life and decrease stress and anxiety levels but also helps patients to better psychologically accept a breast cancer diagnosis.^[^2^,^^3^^]^ Therefore, it is not surprising that the proportion of women who are high risk, including women with comorbidities, women older than 60 years, and women with aggressive types of breast cancer, who opt to undergo breast reconstruction has increased more than threefold since the late 1990s.^[^4^]^

When immediate or two-stage implant-based breast reconstruction is not possible, is declined by the patient, or fails over time, free autologous breast reconstruction is recommended.^[^5^,^^6^^]^ In 2010, 28% of plastic surgeons in the United States reported a preference for performing breast reconstruction using the deep inferior epigastric perforator (DIEP) flap, making it the most important free flap in autologous breast reconstruction.^[^7^]^ The current surgical standard includes end-to-end anastomosis of the DIEP flap artery and the internal mammary artery (IMA) which, unavoidably, leads to complete transection of the distal end of the latter.^[^8^]^

As the makeup of the population changes, with projection studies predicting that future surgical cohorts will be older and more obese, it can be safely assumed that the rates of heart disease will also be higher.^[^9^]^ Furthermore, it is known that radiotherapy can increase the risk of ischemic heart disease, depending on the dose to the heart, particularly in women with preexisting cardiac risk factors.^[^10^,^^11^^]^ Despite a lack of high-level evidence on the proportion of patients who have undergone free autologous DIEP flap breast reconstruction and who developed ischemic heart disease, prior research has cautioned against complete transection of the IMA.^[^12-14^]^ Furthermore, there is evidence indicating that an arterial end-to-end anastomosis may compromise abdominal skin perfusion, thus potentially playing a role in the onset of abdominal wound healing disorders.^[^15^]^

Based on the currently available evidence, we hypothesize that the use of microsurgical end-to-side anastomosis in DIEP flap breast reconstruction surgery is a viable alternative to the standard end-to-end technique. We predict that the less commonly used end-to-side technique is not associated with an increased risk of flap loss, whilst being associated with lower abdominal complication rates. Simultaneously, it allows for the preservation of the IMA for future use as a bypass graft in coronary artery bypass surgery. The DIEP-ES study will be the first pilot study to compare arterial end-to-side and arterial end-to-end anastomosis in DIEP flap breast reconstruction surgery. Given the contradictory results in the literature on the surgical complication rates between arterial end-to-side and end-to-end anastomosis, a prospective pilot study looking at major complication rates is imperative for sample size calculation of large-scale multicenter trials.

## Methods

### Study setting

The DIEP-ES trial will be conducted in the BG Center Ludwigshafen - Department of Hand, Plastic and Reconstructive Surgery.

### Study participants

We include any patients planned for unilateral DIEP flap breast reconstruction who received prophylactic mastectomy or mastectomy due to breast cancer treatment, and who are aged 18 years or above. We exclude any patients with a legal guardian, lack of ability to communicate or capacity to provide consent, and patients with a history of a blood clotting disorder or thrombosis-promoting diseases. By including patients with a history of cancer, we ensure to include the main cohort of patients who tend to receive breast reconstruction. Furthermore, by excluding patients receiving bilateral DIEP flap reconstruction, abdominal skin perfusion is not biased by the type of reconstruction and can be assessed more objectively. Finally, we exclude all patients with blood clotting disorders or thrombosis-promoting secondary disease to avoid any predisposition to complication rates.

### Study design

The study will follow a sequential design starting with patient recruitment. Patients will be screened based on inclusion and exclusion criteria, and those eligible will be randomized into either the end-to-side or end-to-end anastomosis group. The surgical procedure will be performed by experienced surgeons, and patients will be followed up at 2 weeks, 6 weeks, 6 months, and 12 months post-surgery. Data will be collected on primary and secondary outcomes. The study design is detailed in Fig. 1. The success of the surgical techniques will be evaluated using the following objective criteria: (1) Flap viability and complications, assessed through clinical examination, (2) perfusion at the donor-site, assessed using hyperspectral imaging, (3) patient satisfaction, measured using the SF-36 and BREAST-Q questionnaires at multiple time points post-surgery.

**Figure 1. F1:**
[figure not shown]
Study design. DIEP, deep inferior epigastric perforator; DIEA, deep inferior epigastric artery; IMA, internal mammary artery.

### Control(s)/comparator(s)

We chose arterial end-to-end anastomosis of the flap artery, namely the deep epigastric artery, and IMA as the control group since it is a more recently proposed surgical option in DIEP flap breast reconstruction.^[^10^]^ Transection of the IMA may not just impact abdominal skin perfusion, but also compromise future coronary artery bypass surgery, a major reason for the necessity of comparing the newly described arterial end-to-side anastomosis with the well-established arterial end-to-end anastomosis.

### Primary outcomes

The primary outcome is “major complication” at the recipient site, defined as the occurrence of microsurgical complications (anastomotic insufficiency, arterial thrombosis), hematoma, seroma, reoperation, or partial or total flap loss. This was chosen as it is simple but objective, consistent, and easy-to-compare safety outcome.

### Secondary outcomes

The secondary outcomes of abdominal perfusion and major complications of the donor-site, which include abdominal wound healing disorders, were chosen based on the understudied association between transection of the IMA and compromised abdominal wound healing following DIEP flap breast reconstruction. By utilizing hyperspectral imaging to determine perfusion of the abdominal wall, as well as performing frequent clinical assessments of the donor sites’ wound healing, we aim, for the first time, to collect objective prospective data. Moreover, we included patient satisfaction, as evaluated through the SF-36 and the BREAST-Q (reconstructive module) questionnaires, as a secondary outcome. Since lack of satisfaction with the outcomes of mastectomy and implant-based breast reconstruction is one of the main reasons leading patients to seek autologous breast reconstruction, it is important to consider patient satisfaction and physical and psychological well-being.

### Recruitment

Relevant to the proposed project, 517 microsurgical procedures were performed, of which 60 were free autologous breast reconstructions. The BG Center Ludwigshafen holds weekly breast consultation clinics aimed at recruiting patients seeking autologous breast reconstruction. Furthermore, patients are selected at specialist consultation clinic appointments. Our selected recruitment number of 60 patients is well within the number of DIEP procedures performed annually at the BG Center Ludwigshafen and is realistically achievable.

### Treatments/procedures

During the screening visit, written informed consent and patient eligibility will be established. Furthermore, demographic, as well as health-related data, will be collected, and a standardized clinical examination will be performed.

During the baseline visit, laboratory blood tests and a second clinical examination will be performed. Hyperspectral imaging of the abdominal wall will be conducted using the Tivita® tissue camera system, (Diaspective Vision, Am Salzhaff, Germany) to define the baseline abdominal perfusion measurement for each patient. Hyperspectral imaging has been validated in previous research for its accuracy in assessing skin perfusion and related parameters. Lu and Fei reviewed the application of HSI in medical fields and highlighted its ability to capture spatially-resolved spectral data that provides quantitative information on tissue physiology and morphology. In particular, HSI has been successfully utilized to monitor skin conditions, detect ischemic areas, and evaluate tissue oxygenation and blood flow^[^16^]^. To assess the patients’ preoperative health-related quality of life and satisfaction, patients will be asked to fill out the SF-36 and BREAST-Q (reconstructive module) questionnaires. The SF-36 Health Survey is a generic instrument for the assessment of the patient’s health-related quality of life, while the BREAST-Q is a validated questionnaire to measure patient perception before and after breast reconstruction by examining various quality of life domains (psychosocial, physical, and sexual well‐being) and satisfaction domains (satisfaction with breasts, and with outcome).^[^17^,^^18^^]^ Furthermore, preoperative computed tomography angiography (CTA) of the abdominal wall ensures adequate planning for intraoperative perforator dissection.

Post-surgery, hourly clinical flap perfusion controls will be performed and documented for five days. Furthermore, the Tivita® Tissue apparatus will be used to take hyperspectral images to measure flap and donor-site oxyhemoglobin level (Oxy), deoxyhemoglobin level (Deoxy), and oxygen saturation (O_2_Sat). More specifically, the device will be held at a standard, predefined distance from the site of interest, and tissue scan images will be obtained. The images will be electronically stored and analyzed using the company’s algorithm. Patients will be followed up on days 1, 3, and 6, as well at 6 weeks, 6 months, and 12 months with hyperspectral imaging and clinical examination, after 12 months, the SF-36 and BREAST-Q questionnaires will be filled out again.

### Surgical procedure

In all patients, the internal mammary vessels will be rapidly exposed, typically at the 3rd or 4th intercostal space. Following the splitting of the pectoralis major muscle along its fibers and its subsequent retraction, the intercostal muscle layer will be divided using a bipolar electrocautery device. If deemed necessary, the medial portion of the rib cartilage will be removed. Under loupe magnification, the internal mammary vessels will be carefully dissected, and any side branches present will be clipped and divided. After positioning the flap, venous anastomoses will be executed using venous coupler devices, whereas all arterial anastomoses will be performed manually with 8-0 nylon sutures under a microscope.

For end-to-side arterial anastomosis, microvascular clamps will be applied, and an arteriotomy will be created by making an elliptical excision of the arterial wall using scissors. Suturing will begin at the 6-o’clock position (defined as the caudal edge of the excision) and proceed sequentially through the 5-o’clock, 7-o’clock, 4-o’clock, 8-o’clock, 3-o’clock, 9-o’clock, 2-o’clock, 10-o’clock, 1-o’clock, 11-o’clock, and 12-o’clock positions. This approach ensures constant visibility of the arterial lumen, preventing inadvertent fixation of the opposite vascular wall. In end-to-end arterial anastomosis, the IMA will be transected using scissors. Following the transection, suturing will commence at the 6-o’clock position and proceed sequentially as described for the end-to-side anastomosis.

### Frequency and scope of trial visits

A schedule of trial enrolment, interventions, and outcome measurements for each individual patient is presented in Fig. 2. The study’s total duration is anticipated to span 24 months, from first-patient-in (FPI) to last-patient-out (LPO).

**Figure 2. F2:**
[figure not shown]
Frequency and scope of trial visits.

### Serious adverse event reporting

Serious adverse events, not related to the study treatment, are any complications that result in the following: a life-threatening situation, requirement of transfer to an internal medicine department, death, or permanent or significant disability. Patients who experience such adverse events will be excluded from the final analysis. Any serious adverse events will be reported to the ethics committee that approved the protocol, within 7 days of the occurrence of the event.

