### Data monitoring

A pre-selected independent data monitoring committee comprising qualified international experts will monitor compliance with the study protocol and the collected data’s quality.

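### The only definition of a serious adverse event is limited to events unrelated to study treatment, while the reporting sentence covers any such event; whether treatment-related events need the 7-day report is unclear

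*Protocol article*

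**What the plan says.** The section headed Serious adverse event reporting contains three sentences that matter here.

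- Definition: "Serious adverse events, not related to the study treatment, are any complications that result in the following". The listed results are a life-threatening situation, transfer to an internal medicine department, death, and permanent or significant disability.
- Analysis consequence: "Patients who experience such adverse events will be excluded from the final analysis".
- Reporting: "Any serious adverse events will be reported to the ethics committee that approved the protocol, within 7 days of the occurrence of the event".

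No other section defines a serious adverse event, whether related to treatment or not. Under Primary outcomes, the recipient-site endpoint is "defined as the occurrence of microsurgical complications (anastomotic insufficiency, arterial thrombosis), hematoma, seroma, reoperation, or partial or total flap loss". Under Secondary outcomes, major donor-site complications are collected, with abdominal wound healing disorders as the named example. Neither outcome section says to whom, or how quickly, an individual event is reported. The abstract's Conclusions give the purpose of the pilot as evaluating the feasibility and safety of the end-to-side technique.

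**The concern.** Seriousness and causal relation are separate properties of an adverse event. One describes what happened to the patient, the other what is thought to have caused it. The definition merges them, and in the direction that least suits the trial, because it names unrelated events and is silent on related ones. In a comparison of two anastomosis techniques with safety as an aim, a serious event caused by the anastomosis is the event an ethics committee would most need to hear about quickly. If site staff apply the definition literally, that event would not reach the committee through this route. This is not detail that a condensed article leaves to a fuller document. The rule is stated, and it is stated in a form that cannot be applied in only one way.

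**Working it through.** The point concerns wording, so there is no figure to reproduce. The check is to set the three sentences side by side and see what each reading implies for a serious event caused by the anastomosis.

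1. **Definition.** The criteria are attached to events not related to treatment. A related event with the same result, such as death, is neither included nor separately defined.

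2. **Exclusion.** The word *such* points back to the class just defined, so as written this sentence concerns unrelated events.

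3. **Reporting.** The wording changes from *such* to *any*, and the relatedness restriction is not repeated.

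4. **Strict reading.** The reporting sentence uses a term defined two sentences earlier, so *any* means any event meeting that definition. A related serious event is then outside the 7-day report.

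5. **Broad reading.** The change from *such* to *any* is deliberate: unrelated events are singled out for exclusion, and all serious events are reported. A related serious event is then inside the 7-day report. But the only criteria for calling an event serious belong to the unrelated class, so staff have to borrow them.

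6. **Does another section settle it?** The primary outcome captures anastomotic insufficiency, arterial thrombosis, hematoma, seroma, reoperation and flap loss, whatever their cause. The secondary outcomes capture donor-site complications. These sections record endpoints. They set no reporting time and no recipient, and they do not name death, a life-threatening situation, transfer to internal medicine or permanent disability. The Data monitoring section describes no reporting route for individual events. Nothing shown decides between steps 4 and 5.

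7. **Effect of correcting the definition alone.** Suppose the relatedness restriction is deleted and nothing else changes. *Such* in the exclusion sentence would then refer to every serious adverse event. A patient whose death or life-threatening event was caused by the anastomosis would also leave the final analysis. The definition therefore cannot safely be amended without the exclusion sentence.

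**The case against.** The strongest objection is that the reporting sentence says *any*, with no limit, directly after a sentence that says *such*. On plain wording a treatment-related serious event is reportable within 7 days, so it would be wrong to say that it has no route. That stands, and the finding is a mismatch between two sentences, not a proven absence of reporting. It does not remove the problem, because a safety rule should not depend on whether the reader gives weight to a change of pronoun.

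A second objection also stands. The trial's safety evidence is not lost: anastomotic and donor-site complications are study outcomes, supported by hourly flap checks for five days and scheduled examinations to 12 months. What is in doubt is expedited reporting.

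Three stronger inferences are tempting but not supported.

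- *The monitoring committee has no safety role.* The article says that it "will monitor compliance with the study protocol and the collected data’s quality", but does not say that this is all it does. A charter or the full protocol, neither shown, may add a safety remit.
- *Relatedness is judged by staff who know the arm, so counts by arm are biased.* The Methods against bias section says that surgeons and patients are unblinded and that evaluators of post-treatment outcomes follow a blinded regimen. No section says who assigns relatedness.
- *The gap can be sized from the planned rates.* With 30 patients per arm and the rates of 6% and 10% in Power calculations, 30 × 0.06 + 30 × 0.10 = 4.8 complications are expected. At the 1.7% flap-loss rate in the Discussion, 60 × 0.017 ≈ 1.0 flap loss is expected. These count complications and flap losses, not serious adverse events, and many may never meet the listed criteria.

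**Conclusion.** The concern holds as an internal mismatch that has to be corrected. The only definition is restricted to unrelated events, the reporting sentence is not, and no other section shown reconciles them. On the strict reading, a serious event caused by the anastomosis is outside the expedited report. On the broad reading it is inside, but without seriousness criteria of its own. No size can be given, because the document states no serious adverse event rate and no split by relatedness. The weight of the point comes from patient safety and from the trial's own aim, not from an expected count. The conclusion rests on the article as shown. If the full protocol defines these events by seriousness alone, the article's wording still needs to be brought into line with it.

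**What to change.** Make one amendment to the section, with three linked parts.

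1. Define serious adverse events by the listed seriousness criteria alone, and remove the relatedness restriction from the definition.
2. Record relatedness to study treatment as a separate field on the case report form, and state that all serious adverse events, related or not, are reported to the ethics committee within the existing 7 days.
3. In the same amendment, remove or rewrite the sentence that excludes patients with such events from the final analysis, so that the wider definition does not also take treatment-related cases out of it.

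The article reports that enrolment began in February 2023, so events already recorded should be reviewed against the amended definition and any unreported ones submitted. The cost is a short text change, one form field and slightly more reports to the ethics committee.

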### Patient involvement

No patients were involved in the conceptualization of the study, the proposal of the research questions, the design of the study, or patient recruitment.

### Power calculations

Given the nature of this trial (i.e., pilot study) the primary goal is confidence interval (CI) estimation for future studies, rather than formal sample size calculation. Regardless, pilot studies are used to inform sampling decisions for future larger studies. As such, biometric consultation was sought from the Institute of Medical Biometry and Informatics (IMBI), Heidelberg University. Our sample size determination is based on empirical values derived from previous surgical studies, suggesting that a sample size of 60 patients is pragmatic and sufficient for data collection within a feasible timeframe. This approach is supported by guidelines from Lancaster, Dodd, and Williamson, recommending an overall sample size of 30 per group for feasibility and pilot studies with quantitative end goals^[^21^]^. Given a complication rate – as reported by Kim *et al* – of 6% and 10% for end-to-side and end-to-end anastomosis, respectively, the expected confidence interval range is 35.8%^[^22^]^. Assuming a complication rate of 10% in both patient groups, the calculated confidence interval range is 37.6%. Based on the feasibility-study-character of this trial with primarily binary endpoints, such confidence intervals are acceptable. With an estimated enrollment of one patient per week, we expect a total recruitment period of slightly over 12 months. Taking into consideration the 12-month follow-up period, the total duration of this study is estimated to be approximately 24 months, however, the study will continue until the total number of 60 patients enrolled is reached.

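### The two stated confidence-interval widths (35.8% and 37.6%) do not reproduce at the planned 30 patients per group under any standard 95% method tried

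*Protocol article*

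**What the plan says.** All of this stands in the protocol article under Power calculations, unless another section is named.

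- **Sample size.** The text holds that "a sample size of 60 patients is pragmatic and sufficient for data collection within a feasible timeframe". It cites a pilot-study guideline as "recommending an overall sample size of 30 per group for feasibility and pilot studies with quantitative end goals".
- **Purpose.** It states that "the primary goal is confidence interval (CI) estimation for future studies, rather than formal sample size calculation".
- **Precision, first scenario.** For rates "of 6% and 10% for end-to-side and end-to-end anastomosis, respectively", "the expected confidence interval range is 35.8" percent.
- **Precision, second scenario.** "Assuming a complication rate of 10% in both patient groups, the calculated confidence interval range is 37.6" percent.
- **Judgement.** Both widths are called acceptable, given the "feasibility-study-character of this trial with primarily binary endpoints".
- **Losses.** Sixty is the number to be enrolled. No allowance for dropout is given. Serious adverse event reporting foresees removing some patients from the final analysis, but gives no number and no link to the widths.

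The interval method, the confidence level and the per-group n behind the widths are not named. The text does not say explicitly that the interval is for a difference, but one width for each pair of rates leaves little other reading.

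**The concern.** The two widths are the only precision figures in the article, and the article makes interval estimation the main goal of the pilot. A reader will take them as what 30 patients per group can deliver. If they belong to another sample size, the design was judged acceptable on figures that do not describe it. Anyone planning the confirmatory trial also cannot tell whether they refer to 60 analysed patients, to a smaller evaluable set, or to another method. An unnamed method in a condensed article would be no finding. The problem is that two specific numbers are printed and do not follow from the inputs printed with them.

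**Working it through.** **Inputs.** p1 = 6% and p2 = 10% (scenario 1); p1 = p2 = 10% (scenario 2); 60 patients, 30 per group; printed widths 35.8 and 37.6 points (all from Power calculations). Assumption, because the article does not say: two-sided 95% interval for p1 − p2, z = 1.96.

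**Formula (plain Newcombe).** For each group, the Wilson limits l and u are

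[p + z²/(2n) ± z·√(p(1−p)/n + z²/(4n²))] / (1 + z²/n).

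With d = p1 − p2:

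- lower = d − √[(p1 − l1)² + (u2 − p2)²]
- upper = d + √[(u1 − p1)² + (p2 − l2)²]

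**Step 1: reproduce the printed figures.** They come out at n = 25 per group. Wilson limits: 1.40 to 22.32 for 6%; 3.15 to 27.50 for 10%.

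- 6% vs 10%: lower = −4 − √(4.60² + 17.50²) = −22.1; upper = −4 + √(16.32² + 6.85²) = 13.7. Width **35.80**.
- 10% vs 10%: ±√(6.85² + 17.50²) = ±18.8. Width **37.59**.

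Both agree with the print to one decimal. For equal groups the plain-Newcombe match is specific to 25: 24 per group gives 36.7/38.5 and 26 gives 35.0/36.8.

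**Step 2: same method at the planned n = 30.** Wilson limits: 1.56 to 20.43 for 6%; 3.46 to 25.62 for 10%.

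- 6% vs 10%: lower = −4 − √(4.44² + 15.62²) = −20.2; upper = −4 + √(14.43² + 6.54²) = 11.8. Width **32.1**.
- 10% vs 10%: ±√(6.54² + 15.62²) = ±16.9. Width **33.9**.

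Difference from print: 35.8 − 32.1 = 3.7 and 37.6 − 33.9 = 3.7 points.

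**Step 3: other 95% methods at 30 per group.** The Wald width, for example, is 2 × 1.96 × √(p1(1−p1)/30 + p2(1−p2)/30) = 2 × 1.96 × 0.0699 = 27.4 points in scenario 1 and 2 × 1.96 × 0.0775 = 30.4 in scenario 2.

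| Method, n = 30 per group | 6% vs 10% | 10% vs 10% |
|---|---|---|
| Printed | 35.8 | 37.6 |
| Wald | 27.4 | 30.4 |
| Wald, continuity-corrected (two forms) | 34.1 or 40.7 | 37.0 or 43.7 |
| Agresti-Caffo | 30.1 | 32.4 |
| Hauck-Anderson | 31.2 | 34.2 |
| Newcombe | 32.1 | 33.9 |
| Mee | 32.6 | 34.6 |
| Miettinen-Nurminen | 32.9 | 34.9 |
| Clopper-Pearson, combined as in Newcombe | 34.5 | 36.6 |
| Exact unconditional (2/30 or 3/30 vs 3/30 events) | 34.0–34.4 | 35.2–36.8 |
| Newcombe, continuity-corrected | 36.6 | 38.3 |
| The same, width averaged over the binomial distribution | 36.3 | 37.9 |

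No row gives the printed pair.

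**Step 4: other routes to the pair.** Continuity-corrected Newcombe gives 35.84/37.55 at 31 per group, and 35.83/37.57 with groups of 30 and 32; both round to the printed pair, but at 62 patients. For the main methods, unequal splits of 60 were scanned at the 95% level, and equal groups of 15 to 60 at the 80%, 90%, 95% and 99% levels. No combination with 60 patients rounds to both figures. The nearest split is Miettinen-Nurminen with groups of 41 and 19, which gives 35.76/37.53.

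**The case against.** The strongest reply is that the method is unnamed, so nobody outside can say which n was used. The article condenses a full protocol and mentions an external biometric consultation whose calculation is not shown. Continuity-corrected Newcombe reaches the pair at 62 patients, next to the planned 60, and at exactly 30 per group it misses by only 0.7 to 0.8 points (0.3 to 0.5 if the word expected means an average width). This stands against any claim that the calculation was certainly done for 50 patients. It does not rescue the figures, since that method does not give them at 30 per group either.

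Second, fewer than 60 analysed patients is foreseeable because some patients are to be excluded after serious adverse events. That makes a smaller evaluable number plausible, but no figure is given, so it does not explain 25 per group.

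Third, the error does little harm: on the plain Newcombe reading the trial does better than stated, and no test, decision rule or enrolment number depends on it. This stands and limits the severity.

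Two stronger inferences are tempting, and the article supports neither. A reader might conclude that the widths are the only relevant support for 60 patients. But Power calculations also appeals to experience from earlier surgical studies and to pragmatism, and Recruitment to the centre's annual volume; the widths describe the sample size rather than determine it. A reader might also conclude that the pilot-size guideline cannot apply, because it is cited for quantitative goals while the endpoints are mainly binary. That phrase is ambiguous, since estimating a proportion is itself quantitative, and the cited source is not at hand.

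**Conclusion.** The point holds in this form: the printed widths of 35.8 and 37.6 points do not correspond to 30 patients per group under any standard 95% method tried for a difference of two proportions. The size of the discrepancy depends on the method. Under plain Newcombe the printed widths are 3.7 points too wide, which is conservative. Under continuity-corrected Newcombe they are 0.7 to 0.8 points too narrow. Plain Newcombe at 25 per group is an exact match to the printed decimal, but it remains an inference, because continuity-corrected Newcombe at 31 per group also rounds to the same pair. A reader might infer that the trial is less precise than claimed, or that a 50-patient calculation was carried over; the article establishes neither. The conclusion rests on the assumption of a two-sided 95% interval for the difference. Severity is moderate: a stated design figure does not match the stated sample size in a study whose main goal is interval estimation, but nothing in its conduct depends on it.

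**What to change.** In Power calculations, name the interval method, the confidence level and the per-group n, and make the two widths agree with them. Either of these would do:

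- **30 per group intended:** restate both widths for that size. If the Newcombe 95% interval is the chosen method, they are 32.1 points (6% vs 10%) and 33.9 points (10% vs 10%). With another method, use its values.
- **25 evaluable per group intended:** keep 35.8 and 37.6, say that they refer to 25 per group by the Newcombe 95% interval, and state the assumed loss of (60 − 50)/60, about 17%.

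The cost is one corrected sentence and a check against the biometric consultation's calculation. Enrolment does not change.
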